#### Recruitment and participant retention strategies

The recruitment commenced on 31 March 2017 and is ongoing at the time of submission. People with CRPS are recruited through the National CRPS-UK Registry, Oxford University Hospitals NHS Foundation Trust, the Walton Centre NHS Foundation Trust, and other hospitals in the UK by post and clinicians’ referrals. Information about the trial is also disseminated through word of mouth, print and online advertisements and articles, and social media. Trial webpages have been set up on the funder’s and research centre’s websites. All of the above information channels provide potential participants with contact details of the authors, should they be interested in more information and/or taking part in the study.

To promote retention, participants are sent reminders before each RS and LTFU. Since recruitment takes place over a broad geographic area, their travel costs are reimbursed, or the research sessions are conducted in their own home. In recognition of the inconvenience of participation, which is heightened due to the burden of CRPS, participants receive a financial compensation of £250 for their time and contribution to the study once they complete RS4, and further financial compensation once they return the completed LTFU2 questionnaires by post (£50). Healthy control participants are reimbursed for their time and contribution at a rate of £10 per hour of their involvement.

Since the assessments and treatment are non-invasive and do not interfere with the participants’ ongoing standard treatment, and there are potential benefits from taking part, we expect good participant retention. Some participants may directly benefit from reduction in pain and CRPS symptom severity due to treatment. All participants will have an opportunity to undergo the PA treatment after the trial is completed, should the trial support the effectiveness of the treatment.

In the event of the participant’s withdrawal from the study, their data from any completed research sessions will be included in the analysis as far as possible. Participants who withdraw after RS2 will be considered lost to follow-up. For any participant who withdraws before RS4, an additional participant will be recruited to the trial such that there will be 42 full datasets for RS1-RS4. This strategy is implemented to assure sufficient and similar number of participants in each treatment arm. To address any potential selection bias, we will use intention to treat as our primary analysis, and per-protocol as supportive analysis (see “Treatment outcome analyses” section). Should participants deviate from the intervention protocol (e.g., missed treatment sessions), the number of logged treatment sessions can be used as a possible covariate in the final analyses.

### Randomisation

Treatment allocation is conducted by method of randomisation with stratification to minimise baseline (RS1) group differences. Eligible participants with CRPS are allocated in equal numbers to one of the two treatment groups: PA treatment group or sham treatment group. Group allocation is performed using MINIM computer programme [34] by a researcher who is not involved in data collection ([name]). The minimisation procedure controls for the stratification factors that are listed in Table 2. In the event of participant’s withdrawal after treatment allocation, but before RS3, their data shall be removed from the minimisation procedure and an additional participant shall be recruited for the trial to ensure equal numbers of full datasets with any post-intervention data in the two groups.

**Table 2 Tab2:** Criteria for stratification as recorded in RS1

Factor	Weight	Categories
Current pain intensity (0–10 Numerical Rating Scale)	2	≤ 6
		> 6
CRPS severity score (1–16) [35]	2	≤ 12
		> 12
Primarily affected arm	1	Left
		Right
Pre-CRPS dominant hand (writing)	1	Left
		Right
Sex	1	Male
		Female
Age	1	18 - < 40
		40 - < 61
		61–80
Presence of CRPS in body parts other than the primary affected arm	1	Yes
		No
Presence of other non-CRPS pain	1	Yes
		No
CRPS duration	1	< 1 year
		1 - < 5 years
		5 - < 10 years
		≥ 10 years

### Treatment

Participants in the PA treatment group are provided with welding goggles fitted with 35-diopter (∆) Fresnel lenses that induce a visual shift of approximately 19° away from the CRPS-affected side. The optical displacement is of a similar magnitude as in previous CRPS studies that reported significant reductions in pain [22–24]. In contrast, no pain reduction was observed when a CRPS patient underwent 2 weeks of PA using lenses that shifted the visual image only by 5° [24]. Furthermore, prisms strength of 10°-15° was found to be sufficient to induce lasting amelioration of hemispatial neglect after brain injury [14, 17, 18, 36, 37], whereas weaker prisms did not improve neglect [38]. During each treatment session, the participant is seated in front of a vertical surface, such as a wall, upon which an A4 laminated page in landscape orientation is positioned. The page displays two visual targets (red circles 2 cm in diameter), in each top corner. The page is mounted approximately at eye-level, hence targets are located 12.5 cm (approximately 10°) to the left and to the right of the participant’s body midline. The distance between their torso and the wall is established individually, such that the participant can touch the targets with an almost fully extended arm (approximately 60 cm). Participants put on the goggles and use their CRPS-affected arm to perform a total of 50 pointing movements (a number sufficient to induce sensory-motor adaptation [15]), alternating between the two targets (25 per side) and returning the pointing hand to their chest between each movement. The participants are instructed and trained to move as quickly as possible, and the goggles occlude the vision of the participant’s arm for approximately the first half of the movement. Both of these steps limit on-line correction of movement trajectory (strategic component of PA) and reinforce adaptive realignment, which is thought to maximise the effects of PA [12, 39, 40]. One treatment session takes approximately 5 min. The participant performs the treatment once under the guidance of an experimenter, and then twice daily for 2 weeks in a self-guided manner in their own home (giving a total of 29 treatment sessions). The intensity and duration of the treatment regime have been established based on previous studies evaluating the effects of PA on attention in hemispatial neglect following stroke, and on pain in CRPS. In particular, previous studies suggest that repeated sessions of PA are required to obtain a significant reduction in CRPS symptoms [22, 24] and that intense treatment (2 sessions a day for 4 days or more) produces symptom reduction that is sustained for at least 2 weeks post-treatment [22, 23].

Participants in the sham treatment group carry out the same procedure as the PA treatment group, except they are provided with goggles fitted with neutral lenses that do not induce optical deviation of the visual field. This is a standard control treatment for PA [17, 41]. Both prismatic and neutral lenses distort the acuity and clarity of vision, and both sets of goggles occlude the first part of the reaching movement. This factor ensures similarity of the two treatment arms in all aspects of the treatment aside from the sensory-motor adaptation.

To improve their adherence to the treatment protocol the participants receive in-person training, in which they complete the first treatment session guided by [name] or [name], who ensure participants’ competence in performing the exercise according to the protocol. Furthermore, participants are provided with written instructions and a video tutorial. The researcher who trained them in the treatment is also available to address any questions or concerns about the procedure by phone or email. In order to monitor participants’ compliance and adherence, they keep a daily logbook throughout the treatment period, in which they record the time and duration of each treatment session. We will report the adherence to treatment as a percentage of participants in each treatment group who did not miss more than 6 treatment sessions. The extent of exposure in each group will be reported as average number of logged treatment sessions. Protocol deviations are defined as missed or additional treatment sessions, and sessions for which logbook entries suggest that anything other than the trained procedure has been used. We will report the total number of treatment sessions per group in which deviations other than missed or extra sessions are suspected. We will also compare the average number of logged treatment sessions between the two groups, and if significantly different, the number of logged treatment sessions will be used as a covariate in the analyses of the primary outcomes.

The participants are instructed to continue their standard pharmaceutical, physical, and/or other treatments during the trial, and are encouraged not to make any significant alterations to these treatments (e.g., major changes in medication, commencing new physiotherapy programmes). Medications and other treatments are noted during every research session to monitor any changes.

Criteria for discontinuing the allocated treatment before the 2 weeks have elapsed are a participant’s withdrawal from the study, or reports of experiencing an increase in CRPS symptoms that significantly heightens their discomfort or distress. As the treatment procedures require repeated movements of the CRPS-affected arm, participants may experience pain related to movement. However, this is expected to be temporary and no greater than the pain that could accompany standard physiotherapy or daily activities. To date, there have been no publications reporting serious adverse events related to PA in healthy controls or clinical populations (patients with stroke, Parkinson’s disease [41], or CRPS). In one case study exploring the effects of different PA directions and strengths, one CRPS patient experienced a small, temporary increase in pain when they performed PA using optical deviation towards the affected side [24]. Similar events in the current study are highly unlikely, as all PA is conducted with optical deviation away from the CRPS-affected side, i.e., in the direction thought to achieve therapeutic effects. Each participant is assigned their own dedicated set of prism goggles in a bag labelled with their participant code. The direction of optical deviation is independently checked by two people before the goggles are placed in a labelled bag. Any unexpected serious adverse events related to the administration of any study procedures will be reported to the researcher responsible for blinding ([name]) who will then make any decisions about discontinuing an individual’s participation and/or the trial, in consultation with the protocols for dealing with adverse events as outlined by the Research Ethics Committees.

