
**Table 1 Tab1:**
[figure not shown]
Schedule of enrolment, interventions, and assessments for the participants with CRPS

*RS* Research Session, *LTFU* Long Term Follow-Up (postal questionnaires only), *PA* Prism Adaptations

*Primary endpoint of the study

**Secondary endpoint of the study

***Self-reported average levels of pain, range of movement and symptoms interference with daily life in the last 24 h, rated daily on 0–10 Numeric Rating Scales

Deviations from the schedule of consecutive Research Sessions and Follow-Ups will be accepted within the following time windows: up to 2-weeks deferral of RS2 and RS4, up to 1-week deferral of RS3, up to 3-weeks deferral of LTFU1 and LTFU2. If the times that the participant can attend RS2 and RS3 are planned to be longer than 14 days apart, the participant would commence the treatment 2 weeks before RS3. If the participant already started the treatment and has to postpone RS3, they would continue the treatment until RS3.

Twenty-one healthy control participants are being recruited for a single research session to obtain normative data. They undergo testing only once and do not receive any treatment.

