#### Treatment outcome analyses

We will conduct intention to treat (ITT) as our primary analysis to examine the overall effects of prism adaptation. The ITT analysis will include all allocated participants with CRPS regardless of treatment adherence and completion of outcome measurements. Baseline post-randomisation observation (RS2) carried forward will be used to account for missing data in ITT analysis, as the participants are expected to return to pre-treatment baseline over time. The exception is the Patient Global Impression of Change questionnaire that is only completed in the post-treatment research sessions, in which case the RS3 observation will be carried forward. Missing data from the computer-based tasks within each research session will be replaced by group mean for the particular task condition (with an exception of Directional Hypokinesia task, where some participant with CRPS may not be able to complete the task using the affected limb; in such cases only the conditions completed with the unaffected limb will be analysed). Missing daily logbook ratings will be interpolated using linear regression.

We will also conduct a supportive per-protocol (PP) analysis to see whether PA treatment can benefit the participants with CRPS who were able to perform it according to the trained protocol compared to those participants who were able to complete the sham treatment according to trained protocol [111]. The PP population will be the subset of the ITT population who provided complete outcome data for RS1-RS4 (i.e. attended all in-person research sessions and completed the primary outcome measures) and missed no more than 6 treatment sessions.

We will use confidence intervals to compare the RS1 primary outcomes scores of the participants with CRPS who withdrew and those who remained in the trial until RS4 to assess any potential selection bias. The timing and reasons for withdrawal will be presented in a CONSORT diagram.

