#### Efficacy of PA treatment in reducing pain and CRPS symptom severity (RQ1)

A 2 × 6 ANOVA with Group as a between-subjects factor (PA treatment, sham treatment), and Time (RS1, RS2, RS3, RS4, LTFU1, LTFU2) as a within-subject factor will be conducted for the first primary outcome of pain intensity rating. We will also conduct sixteen a-priori contrasts to compare RS1 vs. RS2, RS2 vs. RS3, RS3 vs. RS4, RS2 vs. RS4, RS2 vs. LTFU1, RS4 vs. LTFU1, LTFU1 vs. LTFU2, and RS2 vs. LTFU2 within each group. We will also conduct a 2 × 4 ANOVA with the factors Group (PA treatment, sham treatment) and Time (RS1, RS2, RS3, RS4) for the second primary outcome of CPRS severity score, followed by eight a-priori contrasts comparing RS1 vs. RS2, RS2 vs. RS3, RS3 vs. RS4, and RS2 vs. RS4 within each group. We are primarily interested in detecting any changes between RS2 and RS3 which would represent immediate effects of treatment.

Minimisation factors (see Table 2) may be included as covariates in the ANOVAs if there are significant differences at RS1. Similarly, if we find significant group differences in the Profile of Mood States, Tampa Scale for Kinesiophobia, or Revised Life Orientation Test RS1 scores, these variables may be used as covariates in the ANOVAs on pain and CRPS severity score.

We will also calculate the Number Needed to Treat (NNT) separately for pain and CRPS severity score. The NNT will be based on the proportion of participants in each treatment arm that achieved clinically significant pain relief (≥2 points on 0–10 NRS scale [110]) and reduction in CRPS symptom severity (≥4.9 points [35]) in RS3 compared to RS2.

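### The primary analyses are to be adjusted for logged treatment sessions, a post-randomisation variable, whenever the arms differ on it; this can create or hide a treatment effect

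*Protocol article*

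**What the plan says.** Three places in the protocol bear on this.

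- **Treatment:** mean logged sessions are to be compared across arms, with this consequence: "if significantly different, the number of logged treatment sessions will be used as a covariate in the analyses of the primary outcomes". Once triggered, the adjustment is mandatory, and it is not confined to a sensitivity or supportive analysis.
- **Recruitment and participant retention strategies:** where participants deviate from the intervention protocol, "the number of logged treatment sessions can be used as a possible covariate in the final analyses". Here adjustment is optional and has no significance trigger.
- **Treatment outcome analyses:** intention to treat is primary, and "The ITT analysis will include all allocated participants with CRPS regardless of treatment adherence and completion of outcome measurements". Adherence already has its own supportive per-protocol analysis, limited to participants with complete RS1-RS4 data who missed no more than 6 sessions.

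The target comparison is given under RQ1: "We are primarily interested in detecting any changes between RS2 and RS3".

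**The concern.** A baseline covariate cannot be affected by allocation; a session count can. The protocol itself gives three routes that tie the count to events after randomisation.

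- Treatment may be stopped early on "reports of experiencing an increase in CRPS symptoms that significantly heightens their discomfort or distress", so worsening symptoms can lower the count.
- The note to the schedule in Table 1 adds sessions when the first post-treatment visit slips: "If the participant already started the treatment and has to postpone RS3, they would continue the treatment until RS3".
- The Treatment section describes repeated sessions as needed for symptom reduction, so sessions may carry part of the effect.

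Adjusting for such a variable compares PA and sham participants who logged the same number of sessions. If PA changes adherence, those participants are no longer alike in their underlying pain course, and randomisation no longer protects the comparison. If sessions are part of how PA works, adjustment removes part of the effect. Both primary outcomes are exposed. The other conditional covariates, under RQ1, are measured at RS1 and do not have this fault.

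**Working it through.** **1. Design figures.** The sample size section gives a difference of 2 points, SD 1.98, 5% type I error and 90% power. Taking the test as two-sided:

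n per arm = 2 × (1.960 + 1.282)² × 1.98² / 2² = 2 × 10.51 × 3.920 / 4 = 20.6, so 21 per arm and 42 in total.

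This reproduces the plan. The noncentral t gives 89.1% power at 21 per arm. The planned course is stated as "giving a total of 29 treatment sessions".

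**2. What adjustment does.** Let D be the true group difference in RS2-to-RS3 change (negative favours PA), d the difference in mean sessions (PA minus sham), and r the within-arm correlation between sessions and change. In a model of change on group and sessions, the expected group coefficient is

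adjusted effect = D - b × d, where b = r × SD(change) / SD(sessions).

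Bias therefore needs both d and b to be non-zero. The documents give neither, so both are assumed and varied below.

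**3. Assumption set A.** Latent pain course U has SD 1.4. Change = U + noise of SD 1.4, so SD(change) = √(1.96 + 1.96) = 1.98, matching the protocol. Sessions = 27 + d (PA arm only) - 1.4U + noise of SD 2.

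- Covariance = -1.4 × 1.96 = -2.744.
- Variance of sessions = 1.96 × 1.96 + 4 = 7.842, so SD = 2.80.
- b = -2.744 / 7.842 = -0.350 points per session.
- r = -2.744 / (1.98 × 2.80) = -0.49.
- With D = 0 and d = -3, adjusted effect = 0 - (-0.350)(-3) = -1.05.

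**4. Assumption set B.** SD of sessions is 4, and a shared factor gives r = -0.36 (0.6 × 0.6) or -0.64 (0.8 × 0.8). Then b = -0.36 × 1.98 / 4 = -0.178, or -0.64 × 1.98 / 4 = -0.317.

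**5. The whole procedure with no true effect.** Simulation with 21 per arm: adjust if the t-test on sessions gives p < 0.05, otherwise do not adjust.

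| Set | Gap in sessions | r | Expected adjusted effect | Rule fires | Type I error |
|---|---|---|---|---|---|
| A | 3 fewer | -0.49 | -1.05 | 93% | 36% |
| A | 2 fewer | -0.49 | -0.70 | 61% | 15% |
| A | 1 fewer | -0.49 | -0.35 | 21% | 5.3% |
| A | 0 | -0.49 | 0 | about 5% | about 4% |
| B | 4 fewer | -0.64 | -1.27 | 89% | 57% |
| B | 4 fewer | -0.36 | -0.71 | 88% | 17% |
| B | 2 fewer | -0.36 | -0.36 | 36% | 6.3% |
| B | 4 fewer | 0 | 0 | 89% | 4.3% |
| B | 0 | -0.36 | 0 | 5% | 4.8% |

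The unadjusted analysis rejects in about 5% of trials throughout. Set A lets counts exceed 29. Capping them at 29 lowers 36% to 32-33% and 15% to 13%. With the cap and r about -0.31, a 2-session gap gives 11%. With r about -0.14, a 2-session gap gives 6% and a 3-session gap 8-9%.

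**6. The whole procedure with a true effect of -2.**

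- Set A, PA logs 3 more sessions: adjusted effect = -2 + 1.05 = -0.95. Power falls from about 90% to 34-36% (52% with the cap).
- Set B, r = -0.36, PA logs 4 more: adjusted effect = -2 + 0.71 = -1.29. Power falls from 89% to 52%.
- Half the effect acts through sessions (-1 direct, plus 4 × -0.25 = -1): adjustment leaves about -1. Power falls from 89% to 40%.
- No link to outcome, gap of 4: no bias, but collinearity lowers power from 89% to 80%.

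**The case against.** The strongest reply is that the harm is contingent.

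- **The trigger may not matter.** Both arms share the procedure, training and support, so session counts may barely differ. With a true gap of 0 or 1 session, type I error stays near 5%. This stands as a limit on size, but a rule that is harmless only when it has nothing to correct is not worth keeping.
- **The link to outcome is assumed.** The protocol supports early stopping for marked symptom increase. It does not show that sorer participants skip sessions, and it expects movement pain to be temporary. With a weak correlation the inflation is small. This also stands, and it is why a range is given.
- **The simulated model is not the planned one.** The protocol specifies Group × Time ANOVAs and does not say how the covariate enters. If it enters only as a between-subject main effect, the RS2-to-RS3 group comparison is largely untouched and the rule achieves nothing there. If it acts on change, the bias above applies. Neither reading supports the rule.
- **Intention to treat defines who is included, and a covariate excludes nobody.** That is right about the population. The conflict is with the effect being estimated: the effect of allocation whatever the adherence is not the effect at equal session counts.

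**Conclusion.** The rule is wrong as written. It makes adjustment for a post-randomisation variable mandatory in the primary analyses, with a trigger that responds mainly to an effect of allocation on that variable. The protocol is also inconsistent on whether the adjustment is mandatory or optional.

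The principle is firm; the size is not. Across the assumptions tried, type I error runs from nominal to 57%, and power for a true 2-point effect from 80% down to 34%. Serious harm needs a between-arm gap of roughly 2 or more sessions, a moderate correlation between sessions and change, and a covariate that acts on change. The protocol excludes none of these.

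**What to change.** Remove the session-count covariate from the primary intention-to-treat analyses, and bring the Treatment, Recruitment and participant retention, and Treatment outcome analyses sections into agreement before unblinding. Report logged sessions by arm descriptively, as already planned.

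Keep adherence in supportive analyses labelled as such. The planned per-protocol analysis can serve, with a statement that it too selects on behaviour after randomisation. If an effect of treatment received is wanted, an instrumental-variable (complier-average) estimate with allocation as the instrument is an option, with its assumptions stated. If a session-adjusted model is kept at all, label it exploratory.

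The cost is a text change. The target stays at 42 complete datasets, no new data are needed, and the unadjusted analysis keeps about 89% power.

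### Logged sessions, counted after randomisation and shortened by worsening symptoms, become a covariate in the primary ITT analyses whenever the arms differ on them; the resulting bias can go either way

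*Protocol article*

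**What the plan says.** The Treatment section uses the session count in two ways. The first is descriptive: "The extent of exposure in each group will be reported as average number of logged treatment sessions". The second is a decision rule: the arms are compared on the mean count and, "if significantly different, the number of logged treatment sessions will be used as a covariate in the analyses of the primary outcomes".

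The section on recruitment and retention words the same idea as an option: "the number of logged treatment sessions can be used as a possible covariate in the final analyses". The RQ1 analysis section mentions only RS1 variables, which "may be included as covariates in the ANOVAs if there are significant differences at RS1". It neither repeats nor withdraws the session rule.

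ITT is the primary analysis: "The ITT analysis will include all allocated participants with CRPS regardless of treatment adherence and completion of outcome measurements". For missing values, "Baseline post-randomisation observation (RS2) carried forward will be used to account for missing data in ITT analysis". No text confines the session covariate to the per-protocol or a sensitivity analysis.

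The Treatment section gives two separate reasons for ending treatment early: withdrawal from the study, and "reports of experiencing an increase in CRPS symptoms that significantly heightens their discomfort or distress". The Design section places allocation 1 to 5 days before RS2 and the first session after RS2, so every logged session follows randomisation.

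**The concern.** A covariate in a randomised comparison should be something treatment cannot have changed. The RS1 variables meet that condition and the session count does not. The protocol itself supplies a route from outcome to covariate: pain rises, treatment stops, the count is low. The rule also selects the worst moment to adjust, because the count enters only when it is associated with arm.

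If PA works, more sham than PA participants worsen and stop, sham logs fewer sessions, and the covariate takes over part of PA's effect. If PA participants stop more often for other reasons, such as burden, the adjustment moves the estimate towards an apparent PA benefit. At stake is the headline pain estimate, and likewise CRPS severity, in a trial sized with little power to spare.

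**Working it through.** **Sample size first.** From the sample size section: difference 2 points, SD 1.98, type I error 5%, power 90%. Two-sided normal approximation: n per arm = 2 × (1.96 + 1.28)² × 1.98² / 2² ≈ 20.6, so 21 per arm and 42 in total, as stated. With the t distribution, power at 21 per arm is 89.1%.

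**What the covariate does.** In a linear model of change on arm and sessions, adjusted minus unadjusted effect = -(within-arm slope of pain change on sessions) × (PA minus sham difference in mean sessions). If worsening cuts sessions, the slope is negative. The sign of the session gap then sets the direction:
- PA logs more sessions: the shift is positive and a PA benefit shrinks.
- PA logs fewer sessions: the shift is negative and a benefit is enlarged or created.

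**Smallest gap that triggers the rule** at 21 per arm: 2.02 × SD × √(2/21) = 1.9, 3.1 or 4.4 sessions for an assumed session SD of 3, 5 or 7. At an assumed slope of -0.1 point per session, that alone shifts the estimate by 0.19, 0.31 or 0.44 points.

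**Simulation when PA works** (6000 trials per scenario). Assumed: change RS3 - RS2 is normal with SD 1.98 and mean -2 on PA, 0 on sham. Participants whose pain rises by the threshold stop after 5 to 15 sessions, others miss about 2, and all attend RS3. A t-test on sessions at 0.05 decides whether sessions join arm in the regression. Stopping rates follow from the normal distribution; for 2 points, sham 1 - Φ(2/1.98) = 16% and PA 1 - Φ(4/1.98) = 2%.

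| Stop at rise of | Stopping, sham / PA | Rule triggered | Estimate when triggered, unadjusted to adjusted | Shift | Overall power |
|---|---|---|---|---|---|
| 2 points | 16% / 2% | 26% | -2.40 to -1.60 | 0.80 | 89% to 84% |
| 3 points | 6% / 1% | 7% | -2.32 to -1.76 | 0.56 | 88% to 88% |
| 1 point (low bar) | 31% / 6% | 53% | -2.28 to -1.26 | 1.02 | 89% to 72% |

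The unadjusted means exceed 2 in size because triggered trials are those in which sham happened to do worse. Check of the identity in the last row: slope -0.184, gap 5.58, shift = 0.184 × 5.58 = 1.03, which agrees to rounding.

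**Weaker links.**
- Stopping driven by interim pain correlated 0.5 with the RS3 change (assumed): -2.16 to -1.76 at 2 points (shift 0.40, power 89% to 86%) and -2.23 to -1.96 at 3 points (shift 0.27, no material power loss).
- All stoppers withdraw and RS2 is carried forward (26 per arm, 2-point threshold): -1.66 to -1.53 when triggered (shift 0.13), overall power 91% to 88%.

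**The other direction.**
- No true effect, and some PA participants also stop for unrelated reasons. With 10% to 30% doing so, overall rejection is 3.5% to 6.1%, although at 30% the mean estimate already drifts to about -0.24 to -0.30. With 50%, rejection is about 15% for thresholds of 1 or 2 points (lower at 3 points), and the mean estimate drifts to about -0.6.
- PA costs 4 sessions and each session lowers pain by 0.1 point (both assumed): the total effect is -1.65 and the rule reports -1.98 on average.

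**The case against.** The strongest case against concerns size, not principle.

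- **Stopping bar.** The protocol requires an increase that significantly heightens discomfort or distress, expects movement pain to be temporary, treats 2 points as clinically significant and anticipates 20% drop-out. A reader might infer from the 1-point row that the rule costs about 17 points of power (89% to 72%). The documents do not support so low a bar. This stands, and the 2- and 3-point rows are the ones to use.
- **Deterministic link.** Letting the final pain change decide stopping overstates the link. This stands; with interim pain the shift roughly halves.
- **Withdrawal.** Under Blinding, a participant whose worsening causes concern may be unblinded and then gives no further data, so RS2 is carried forward. This stands for some participants. Since symptom increase and withdrawal are listed as separate reasons to stop, others can stop treatment and still attend RS3.
- **Model.** The plan specifies 2 × 6 and 2 × 4 ANOVAs. A session covariate entered only as a main effect would leave the Group by Time comparison unchanged; a shift needs a covariate-by-time term. The article does not say which is meant, so the change-score figures are illustrations.
- **Conflict with ITT.** A reader might infer that including everyone irrespective of adherence flatly contradicts the rule. It does not: that sentence fixes who is analysed, not the model. The conflict is with what ITT is for.
- **Optional against binding wording.** The general option and the specific rule can be read together. This is at most a difference of wording.

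**Conclusion.** Wrong as written. The protocol binds a post-randomisation count, which symptoms can shorten, to the primary-outcome analyses, and nothing restricts the rule to supportive analyses.

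The size is conditional. On the stated assumptions (21 per arm, effect -2, SD of change 1.98, change-score model, RS3 attended), stopping at 2 or 3 points triggers the rule in about 26% or 7% of trials. In those trials the estimate moves by about 0.6 to 0.8 points, or about 0.3 to 0.4 if stopping follows interim pain. Overall power goes from about 88-90% to 84-88%. If all stoppers withdraw, the shift is about 0.1 point and power falls by about 3 percentage points. If the test on sessions is not significant, the primary model is unchanged.

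Two stronger readings are tempting. One is that the rule only ever hides a PA benefit; the direction depends on which arm logs fewer sessions. The other is a general statement about type I error, reassuring or alarming. Rejection stays near 5% with 10% to 30% unrelated PA stopping and reaches about 15% at 50%. One more extreme assumed scenario (PA costs 4 sessions, and each point of pain costs one more) gives 46%. The documents give no rates with which to choose among these.

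**What to change.** In the Treatment section, replace the covariate clause with: *Logged sessions will be reported and compared by arm and will not enter the ITT analyses of the primary outcomes.*

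In the recruitment and retention section, limit logged sessions as a covariate to an analysis labelled exploratory (dose-response). The adherence question stays with the per-protocol analysis already planned.

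The cost is wording in two places, with no new data, visits or sample size. The downside is that a real difference in dose would be described and explored but not adjusted for in the primary result.
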